#### *Number of patients*

In order to achieve a total number of  $n=200$  ( $n=50$  per treatment arm) at the end of the study, we will initially include 270 patients.

#### *Withdrawal of patients*

The patients are free to discontinue their participation in the study at any time and without prejudice to further treatment. The patient's participation in the study can be discontinued at any time at the discretion of the investigator. Justifiable reasons to discontinue a patient from the double blind treatment of the study include: the development of a serious adverse event, non-compliance of the patient, erroneous inclusion of the patient in the trial, acute exacerbations requiring oral steroid treatment (see below) for  $> 3$  periods during the past 12 months or  $> 2$  periods during the past 3 months, any treatment not allowed in the study, development of a concomitant disease that interferes with the interpretation of the study, withdrawal of consent. Patients who discontinue their participation in the study will be contacted by the investigator to obtain information about the reason for discontinuation. The reasons for study discontinuation will be reported on a study-termination form.

An effort will be made to collect as many data as possible on the outcome variables after withdrawal, so that the reasons for withdrawal can be analysed to check for bias.

#### *Postponing visits in case of exacerbations*

Any period requiring a short course of oral steroids (30 mg prednison for 6 days), given at the

discretion of the physician, will be labelled as an acute exacerbation. Study visits will have to be postponed if such oral course of steroids has been given < 8 weeks prior to the visit (12 weeks in case the visit will include a bronchoscopy. The next visit has to be scheduled at the next predefined time point according to the regular 3 monthly intervals.

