## Hypothesis

We hypothesize that inhaled steroid treatment in patients with COPD leads to the following:

1. An initial improvement in symptoms, quality of life, and FEV1, associated with a reduction in features of airways inflammation.
2. 6 Months of treatment will be sufficient to maintain these initial effects; continuation of therapy beyond 6 months will lead to an unfavourable balance between destruction and repair within the airway wall.
3. After the initial improvement, the increased annual decline in FEV1 continues, which is associated with on-going airway remodelling and parenchymal destruction.
4. Airway hyperresponsiveness, elevated serum IgE, Th2 cytokine profile, and eosinophil infiltration are predictive of the initial benefits on symptoms, FEV1, and airway inflammation.
5. Addition of a long-acting  $\beta$ 2-agonist to inhaled steroid treatment augments the benefit of therapy with regard to symptoms and quality of life, without changing the decline in FEV1 or the pathological outcome.

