## Aim

The aim of the present study is to test the above hypotheses by comparing the clinical, functional and pathological benefits of:

- short-term (6 months) inhaled fluticasone followed by placebo (24 months)
- long-term (30 months) inhaled fluticasone
- long-term (30 months) salmeterol + inhaled fluticasone
- long-term (30 months) placebo

in a double blind, randomised, controlled trial in patients with COPD.

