## Study design

In this prospective, longitudinal, double blind study COPD patients will be followed up for 2.5 years (see *figure*). The study begins as a 3 groups parallel design during 6 months, followed by a 4 groups parallel design during 24 months. The aim is to finish the study with 50 patients in each of the 4 parallel groups at 30 months.

Patients will be treated by the investigator-physician with inhaled corticosteroids (500 µg b.i.d. fluticasone by DiscusR), or inhaled corticosteroids with long-acting  $\beta_2$ -agonist (+ 50 µg b.i.d. salmeterol), or a matching placebo for the first 6 months. Thereafter, half of the corticosteroid group will continue and the other half will receive placebo for 2 years. The patients who will be treated with placebo or inhaled corticosteroids + salmeterol continue their treatment during the complete period of 2.5 years. Rescue treatment will be on demand usage of inhaled inpratropium bromide, which is a standard bronchodilator in COPD [Siafakas 1995].

Subjects who fulfil all inclusion criteria and none of the exclusion criteria (see patient selection) will be allocated to receive placebo, inhaled corticosteroids (equivalents of 500 µg b.i.d. = 1000 µg fluticasone) or inhaled corticosteroids + salmeterol at the beginning of the study using the minimization method. The use of minimization will provide treatment groups that are closely balanced for a number of variables (centre, gender, current smoker, FEV1/IVC < 60%, PC20 methacholine < 2 mg/ml), which might influence the primary and secondary outcome variables [Altman 1995]. The first patient is given a treatment at random. For each subsequent patient we will determine which treatment will lead to better balance between the groups with respect to centre, gender, smoking, FEV1/IVC and PC20. The group with inhaled steroid will be randomly allocated to either the steroid group or the placebo group after 6 months of steroid treatment. Minimization will be performed using a computerized method [Pocock 1983].

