## Measurements

Measurements of symptoms, QOL, and spirometry (postbronchodilator) will be made every 3 months. In addition, exhaled nitric oxide (NO), bodyplethysmography and carbon-monoxide diffusion capacity will be measured at 0, 6 and 30 months. Bronchial biopsies, bronchoalveolar lavage, and sputum induction will also be performed at 0, 6 and 30 months. Peripheral blood eosinophils, IgE, and PC20 methacholine at 0, 6 and 30 months. In bronchial biopsies,

bronchoalveolar lavage and sputum special attention will be paid to the number of lymphocytes, neutrophils, eosinophils, macrophages, mast cells, and the state of activation of these cells and the epithelium.

Once during the study a spiral computed tomography (CT-scan) will be performed to quantify the presence of pulmonary emphysema in each patient [Gevenois 1996], and EDTA-anti-coagulated whole blood will be collected for DNA-isolation, for future studies on gene polymorphisms possibly associated with glucocorticoid responsiveness or other study outcomes.

The effects of treatment will be analysed by relating the observed changes in clinical and pathophysiological outcome, to those in cellular and histological outcome (see analysis).

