### *Blinding*

All study medication, active drugs and placebo will be of identical appearance throughout the study. The study inhalers will be labelled identically with centre code and subject number.

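### A month-6 bronchoscopy postponed for a recent oral-steroid course is not tied to the drug switch, so the stop arm's only planned on-steroid biopsy can be taken on placebo

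*Protocol*

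**What the plan says.** **The switch.** The section Study design states: "The group with inhaled steroid will be randomly allocated to either the steroid group or the placebo group after 6 months of steroid treatment". It also states: "Thereafter, half of the corticosteroid group will continue and the other half will receive placebo for 2 years". The Aim describes this arm as 6 months of fluticasone and then 24 months of placebo.

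**The biopsies.** The Measurements section states: "Bronchial biopsies, bronchoalveolar lavage, and sputum induction will also be performed at 0, 6 and 30 months". Inflammatory cells in these biopsies are the primary outcome.

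**Postponement.** Under Postponing visits in case of exacerbations: "Study visits will have to be postponed if such oral course of steroids has been given < 8 weeks prior to the visit". The limit is 12 weeks when the visit includes a bronchoscopy. The section ends: "The next visit has to be scheduled at the next predefined time point according to the regular 3 monthly intervals".

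**Blinding.** "The study inhalers will be labelled identically with centre code and subject number".

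**Analysis.** The section Statistical analyses compares changes in cell counts over time by treatment group, with linear mixed effects models, and counts time from the baseline visit.

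**The concern.** The washout before a bronchoscopy is sensible, because a recent oral course would itself alter the cell counts. The gap is that the washout moves the biopsy and no rule moves the drug.

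In three of the four arms this does no harm of this kind, since the study drug is the same before and after month 6. In the arm that stops fluticasone, a postponed biopsy can fall in the placebo phase. For that arm month 6 is the only biopsy planned on steroid. It serves twice: as the end of the steroid phase (the initial reduction in inflammation, hypothesis 1) and as the start of the withdrawal phase (hypothesis 2: "6 Months of treatment will be sufficient to maintain these initial effects"). If some of the effect has faded by the time of a late biopsy, the 6-month effect looks smaller. Any later change measured from that biopsy looks smaller too, and little change after stopping is what hypothesis 2 predicts. The patients concerned are not a random subset, because each has had a recent exacerbation.

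An analysis plan can identify such biopsies, but it cannot supply an on-steroid sample that was never taken.

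**Working it through.** **1. The timing rules side by side**

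| Event | What fixes it | Moves after an oral course? |
|---|---|---|
| Month-6 bronchoscopy | Visit schedule and 12-week washout | Yes, mandatory |
| Start of second phase | 6 months of steroid treatment | Nothing says so |

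The final sentence of the postponement section can be read in two ways:

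- The postponed visit goes to the next 3-monthly slot. The biopsy is at month 9, 52.18/4 = 13.0 weeks after the nominal switch.
- Only the following visit keeps its date. The biopsy waits until 12 weeks after the course, 0 to 12 weeks after month 6.

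On both readings the biopsy falls after month 6. An oral course between about week 14 and week 26 sets this off.

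**2. How many patients**

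The protocol gives no exacerbation rate. I assume 0.2, 0.4 or 0.8 oral courses per patient-year at a constant rate. The chance of at least one course in the 12 weeks before month 6 is p = 1 − exp(−rate × 12/52). The stop arm is about 270/4 = 67 enrolled, or 50 completers as targeted.

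| Assumed rate | p | Of 67 enrolled | Of 50 completers | Of all 270 |
|---|---|---|---|---|
| 0.2 | 0.0451 | 3.0 | 2.3 | 12.2 |
| 0.4 | 0.0882 | 5.9 | 4.4 | 23.8 |
| 0.8 | 0.1686 | 11.3 | 8.4 | 45.5 |

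The mean wait until 12 weeks have passed since the last course (truncated exponential) is 6.05, 6.09 or 6.18 weeks.

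**3. A bound on the distortion, for illustration only**

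The protocol's detectable difference of 1.62-fold reproduces. With SD ln 2.34 = 0.850, 50 per arm, two-sided alpha 0.05 and power 0.80, the normal approximation gives exp(2.80 × 0.850 × √(2/50)) = 1.61, and the noncentral t gives 1.62.

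Suppose the true stop-versus-continue difference in change from month 6 to month 30 is 1.62-fold, and that a share f of it has already been lost at each postponed biopsy. A simple two-point change then shows exp(ln 1.62 × (1 − p × f)):

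| Assumed rate | f = 1 (all lost) | f = 0.5 | f = 0 |
|---|---|---|---|
| 0.2 | 1.59 | 1.60 | 1.62 |
| 0.4 | 1.55 | 1.59 | 1.62 |
| 0.8 | 1.49 | 1.56 | 1.62 |

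For pooled fluticasone against placebo at month 6, half the fluticasone patients are in the stop arm. Even with f = 1 a true 1.62 reads exp(ln 1.62 × (1 − p/2)) = 1.60, 1.59 or 1.56.

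These figures need an assumed rate, an assumed fade and a two-point change score. The protocol gives none of the three, so they limit the size of the problem and do not estimate it.

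**The case against.** **The gap is one of silence.** The word after sets an order and a nominal length. A switch made just after a delayed bronchoscopy is still after 6 months of steroid, and the durations in the Aim can be taken as nominal labels. This stands in part. A reader might infer that two rules flatly contradict each other, so that one must be broken whatever the site does. The text does not go that far, since it permits a later switch. It does not require one, however, and the only trigger it states is time on steroid.

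**Sites may tie new supply to the completed visit.** They may. Identical labelling shows that sites are blinded, not that placebo is issued on a fixed date. Equally, a site that simply continues dispensing cannot see when the contents change, so the blind gives no protection.

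**The late biopsy is not relabelled as month 6.** This stands. A reader might infer that it is counted as the month-6 value, but the analysis section uses elapsed time and also requires evaluability decisions before the code is broken. Elapsed time with treatment group records the later date, not the change of drug. It therefore leaves the sample ambiguous unless treatment at biopsy is also used.

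**The size is unknown.** This stands. A reader might infer a loss of power or a material bias. The documents support neither, because they give no exacerbation rate and no speed of fading. The stop-versus-continue contrast is also unaffected if change is measured from month 0.

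**Month 30.** A reader might extend the point to the last bronchoscopy. No rule changes the drug there, so the documents do not support that.

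**Conclusion.** The point holds as a gap between two rules. Postponement of a month-6 bronchoscopy is mandatory after a recent oral course, and nothing makes the switch to placebo wait. Followed as written, a stop-arm patient with a postponed biopsy provides the on-steroid sample up to about 13 weeks into placebo.

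The effect is likely to be small. On the assumed rates it concerns 4.5% to 16.9% of the stop arm, about 3 to 11 of some 67 enrolled or 2 to 8 of 50 completers. The bias is nil if the steroid effect has not faded by then, and no loss of power is claimed. It is a cheap improvement worth making, because the missing sample cannot be recovered at analysis.

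**What to change.** **In Study design:** state that second-phase medication is released after the month-6 bronchoscopy.

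**In Postponing visits in case of exacerbations, add:**

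- When the month-6 bronchoscopy is postponed, every patient, whatever the arm, stays on first-phase medication until it is done. Applying this to all arms keeps the blind.
- The bronchoscopy is done as soon as 12 weeks have passed since the course. First-phase medication continues to month 9 at the latest.
- Any biopsy taken after the switch is analysed by the treatment being received at the time, not as the on-steroid 6-month value.
- If no month-6 bronchoscopy will be done, the second phase starts at month 6.

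No change is needed at month 30.

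**Cost.** A few lines of text and a reserve of first-phase inhalers. On the assumed rates about 12, 24 or 46 of 270 patients would wait, in total 270 × p × mean wait = 74, 145 or 281 patient-weeks. In the few stop-arm patients concerned the steroid phase is about 6 weeks longer on average and at most 13. The 6 and 24 months in the Aim become nominal for them, which is a smaller departure than a biopsy on the wrong drug. Biopsies still blocked at month 9 should be rare: at a constant rate at most p² = 0.2%, 0.8% or 2.8%. No patients or procedures are added.

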### *Blinding*

All study medication, active drugs and placebo will be of identical appearance throughout the study. The study inhalers will be labelled identically with centre code and subject number.

### *Treatment compliance*

Patients are required to comply with the treatment regimens throughout participation in the study. Compliance will be checked by counting the doses on the Discus inhaler. A minimum of on average 70% of the treatment dose must have been taken in order to include a patient in the analysis.

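### The 70% compliance gate averages doses with no stated period, which does not fit a design that switches treatment at month 6 and takes primary biopsies at months 6 and 30

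*Protocol*

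**What the plan says.** The rule is in the protocol under Treatment compliance. It opens with a general duty: "Patients are required to comply with the treatment regimens throughout participation in the study". It then gives the measurement: "Compliance will be checked by counting the doses on the Discus inhaler". Finally it sets the gate: "A minimum of on average 70% of the treatment dose must have been taken in order to include a patient in the analysis". No period, phase or weighting is attached to the average, and no other section supplies one.

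The design elements that the rule must fit are elsewhere in the protocol:

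- Aim defines the short-term arm as "short-term (6 months) inhaled fluticasone followed by placebo (24 months" and the comparison arm as "long-term (30 months) inhaled fluticasone".
- Study design describes the month-6 switch: "half of the corticosteroid group will continue and the other half will receive placebo for 2 years". The active regimen is "500 µg b.i.d. fluticasone by Discus".
- Measurements sets the timing of the primary outcome: "Bronchial biopsies, bronchoalveolar lavage, and sputum induction will also be performed at 0, 6 and 30 months".
- Blinding says that active and placebo inhalers look identical throughout, so the dose counter treats both alike.
- Statistical analyses requires all evaluability decisions to be made before the treatment code is broken.

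**The concern.** A compliance gate is meant to show that a patient received the treatment of the arm before the measurement being analysed. A single undated average cannot do that here, for three reasons.

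First, most doses in the short-term arm are placebo, so the average mainly measures placebo use. The second hypothesis asks whether six months of active drug is enough, so exposure in those six months is what matters.

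Second, one decision governs both biopsy time points. Whether a month-6 biopsy is analysed then depends on behaviour after it was taken.

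Third, the average ignores when doses were missed. A long-term patient can have stopped well before the month-30 biopsy and still count as continuously treated.

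The point here is how compliance is derived. Whether non-compliers should be excluded from the main analysis at all is a separate question.

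**Working it through.** The plan gives no calculated compliance figure to reproduce; 70% is a rule. The check applies that rule to the plan's own durations.

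**Inputs.** Threshold 0.70 (Treatment compliance). Short-term arm: 6 months fluticasone, then 24 months placebo. Long-term arm: 30 months fluticasone (both from Aim). Assumptions: the patient completes 30 months, and dosing frequency is the same in both phases, so share of doses equals share of months.

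**Formula.** With a the share of doses taken in months 0–6 and b the share in months 6–30:

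average = (6a + 24b)/30 = 0.20a + 0.80b, compared with 0.70.

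**Short-term arm**

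- No fluticasone (a = 0): passes if b ≥ 0.70/0.80 = 0.875. Example: b = 0.88 gives 0.704, included.
- All fluticasone (a = 1): fails if b < (0.70 − 0.20)/0.80 = 0.625. Example: b = 0.60 gives 0.68, excluded.

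**Month-6 data, any arm.** The second example is excluded although every dose before the month-6 biopsy was taken. The same arithmetic holds in all arms: 80% of the weight in a decision about month-6 data comes from doses due after month 6.

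**Long-term arm, gap before month 30.** If a share p of doses is taken until the patient stops, the longest terminal gap that passes is 30 − 21/p months.

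| Prior use p | Longest gap that passes (months) |
|---|---|
| 100% | 9.0 |
| 95% | 7.9 |
| 90% | 6.7 |
| 85% | 5.3 |
| 80% | 3.8 |

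**How often, under assumed adherence.** The protocol gives no adherence data. Three settings were simulated for the short-term arm (400,000 draws each, bivariate normal, clipped to 0–100%).

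| | Setting A | Setting B | Setting C |
|---|---|---|---|
| Mean use, months 0–6 / 6–30 | 85% / 75% | 80% / 70% | 90% / 80% |
| SD; correlation | 20 points; 0.6 | 25 points; 0.5 | 15 points; 0.7 |
| Pass with under 70% of fluticasone | 5% | 8% | 2% |
| Fail with at least 70% of fluticasone | 18% | 21% | 13% |
| Retained by the single average | 64.4% | 53.1% | 80.1% |
| Retained by months 0–6 ≥ 70% | 77.3% | 65.6% | 90.9% |
| Retained by both phases ≥ 70% | 54.0% | 40.6% | 72.8% |

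These are three points, not a range. Varying mean, SD and correlation independently within the same limits gives 0.4–13% for the first misclassification row and 7.5–31% for the second.

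**The case against.** **The period is an inference.** The text never says that the average runs over 30 months, and an analysis plan that is not shown may define it. This stands as a caveat. But the protocol itself states the gate, as one decision on entry to the analysis, next to a duty to comply throughout participation. Whole-study is therefore the plain reading. If another period is meant, the rule should say so.

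**The examples are extreme.** This is largely right. In the three settings essentially nobody passes with 5% or less of the fluticasone taken, and at most about 0.15% pass with under 35%. Most of the 2–8% lie near the threshold. The 9-month gap needs perfect use for 21 months and sits exactly on the cut-off. A reader might infer that the analysis set would hold many untreated patients; the documents do not support that.

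**The direction of bias.** A reader might infer that all three faults shrink the difference between stopping and continuing. Only the terminal gap clearly does, because it makes a long-term patient resemble a stopper. Excluding a patient who took the full course and then stopped using placebo costs numbers but does not dilute exposure. A never-treated patient in the short-term arm turns the comparison into continuing versus never treated, which could enlarge the contrast if six months leaves lasting benefit.

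**A two-phase rule does not rescue everyone.** Also right. If a ≥ 0.70 and b ≥ 0.70, the average cannot be below 0.70. So anyone who fails the average with at least 70% of fluticasone has b < 0.70, and fails a two-phase rule at month 30 as well. Judging the short-term arm on months 0–6 alone would avoid this, but it needs the treatment code and sets different exclusions in the arms being compared.

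**Investigators may discontinue non-compliers.** That power, under Withdrawal of patients, is discretionary and has no threshold or period, so it does not close the gap.

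**Conclusion.** The point holds as a fault in how the compliance value is defined. On the plain reading, and with equal dosing frequency in both phases, these results follow from the protocol's own durations: fluticasone weighs 0.20 in the short-term arm; the pass and fail limits on placebo use are 87.5% and 62.5%; month-6 data are selected on later doses in every arm; and a terminal gap of up to 9 months passes in the long-term arm.

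The frequencies are illustrative only, since they rest on assumed adherence. The most secure consequence is at month 6, where conditioning on later behaviour serves no purpose and can be removed without new data. At month 30 the secure consequence is the undetected gap off drug. The change is worth making, but nothing here shows that the trial's conclusions would be reversed.

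**What to change.** Replace the single average under Treatment compliance by compliance per phase, from the same dose counts and identically in all arms. It needs only dates and counts, so it can be applied before the code is broken.

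- **Month-6 analyses:** apply the 70% criterion to months 0–6 only. The patient with all fluticasone and 60% placebo use is kept; the patient with no fluticasone is not.
- **Month-30 analyses:** report compliance for months 0–6 and 6–30 separately. Use at least 70% in each phase only to define a supportive compliant set, not to restrict the main month-30 comparison. The 9-month stopper then has 15/24 = 62.5% in months 6–30 and falls outside that set.
- Do not add an arm-specific rule or a compulsory criterion for the last three months before the bronchoscopy.

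**Cost.** Dose counts must be tabulated by interval; visits are already three-monthly. In the three settings the month-6 criterion keeps more of the short-term arm than the single average does, though that would not hold if early use were poorer than later use. The month-30 compliant set is noticeably smaller, by 10.4, 12.5 and 7.3 percentage points, which matters in a trial aiming for 50 per arm and is why it should be supportive only. The two-phase criterion also shortens the terminal gap without removing it: with full prior use, 0.30 × 24 = 7.2 months could still pass. Reporting dose counts by interval would make such gaps visible.

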### *Statistical analyses*

Prior to breaking the treatment code at the end of the study, all decisions on the evaluability of data from each individual patient for the statistical analyses are made and documented. The effects of treatment will be analysed according to treatment group. Primary analyses will be comparing changes in cell counts per treatment group in time. Secondary analyses will compare changes in clinical outcome variables such as lung function and respiratory symptoms with changes in cell counts.

Linear mixed effects models will be used to estimate the effects of treatment on changes in primary outcome variables (cell counts) and the secondary outcome variables (such as lung function, bronchial hyperresponsiveness, number of blood eosinophil count). Graphical visual inspection will be used to determine which model has the best fit (linear/non-linear model). Descriptive statistics will be presented by visit. Confidence intervals will be computed using a 95% confidence interval level and p-values <0.05 are considered to be statistically significant.

In addition, the baseline values of lung function, bronchial biopsy, bronchoalveolar lavage and sputum induction will be evaluated as possible explanatory variables for the outcome. Smoking habits will be evaluated as the duration of smoking (years), average daily consumption prior to the study, average daily consumption during the periods between visits, previous cigarette consumption expressed as packyears.

Time points will be calculated as time elapsed since baseline visit.

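### A 70% dose-taking rule decides who enters the only analysis population the protocol defines, so the primary comparison is not between the groups as randomised

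*Protocol*

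**What the plan says.** Treatment compliance sets the condition: "A minimum of on average 70% of the treatment dose must have been taken in order to include a patient in the analysis". The measure is a dose count: "Compliance will be checked by counting the doses on the Discus inhaler". No averaging period is given.

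Statistical analyses describes the main comparison: "Primary analyses will be comparing changes in cell counts per treatment group in time". On grouping it says: "The effects of treatment will be analysed according to treatment group". It also says that, before the code is broken, "all decisions on the evaluability of data from each individual patient for the statistical analyses are made and documented". Nowhere does the protocol define an all-randomised population or confine the 70% rule to a secondary analysis.

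Withdrawal of patients lists, among the acceptable grounds for taking a patient off blinded treatment, "non-compliance of the patient, erroneous inclusion of the patient in the trial". It adds: "An effort will be made to collect as many data as possible on the outcome variables after withdrawal". The one purpose given for those data is to examine the reasons for leaving as a possible source of bias.

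Study design describes a two-stage allocation. Patients first go by minimisation to placebo, fluticasone, or fluticasone plus salmeterol. Then: "The group with inhaled steroid will be randomly allocated to either the steroid group or the placebo group after 6 months of steroid treatment".

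**The concern.** Minimisation and the random split at month 6 make the groups comparable at the moment of allocation. A filter on doses taken operates after that moment. Treatment can plausibly affect dose-taking through tolerability, perceived lack of benefit, or the blinded change from fluticasone to placebo. If the arms lose different shares of patients, or different kinds of patients, the remaining groups differ in prognosis and the difference in cell counts is no longer purely a treatment effect.

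The primary inference is at stake. The rule says who is in the analysis, and the protocol describes only one. A mixed model cannot recover patients removed before it is fitted.

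The missing averaging period is a second weakness. Compliance could be averaged over months 0 to 6, months 6 to 30, or the whole time in the study. These give different patient sets, and the 0-6 month comparison and the comparison after the switch need not use the same one.

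**Working it through.** **Inputs from the protocol (Determination of the sample size; Statistical analyses).** SD of 2.34-fold, so ln 2.34 = 0.850, or log2 2.34 = 1.2265 doublings. There are 50 patients per arm and a detectable ratio of 1.62, so ln 1.62 = 0.482, or 0.696 doublings. Alpha is 0.05, taken as two-sided. Power of 0.80 is stated for the within-group calculation and assumed to apply here.

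**The plan's own figure.** Detectable ratio = exp[(1.960 + 0.842) × 0.850 × √(2/50)] = 1.610 by the normal approximation, and 1.618 with the noncentral t. The stated 1.62 is reproduced. The defect lies in the analysis population, not in the sample-size arithmetic.

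**Shift caused by exclusion.** The protocol gives no adherence figures, so the inputs here are assumptions. If a share p of an arm is removed, and those removed differ by d SDs from those kept, the mean of those kept differs from the full-arm mean by p × d × SD. With the same d in two arms, the contrast moves by (p1 − p2) × d × SD.

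- p1 = 0.30, p2 = 0.10, d = 0.5: 0.20 × 0.5 × 1.2265 = 0.12 doublings, a ratio of 1.09.
- Same shares, d = 1.0: 0.20 × 1.0 × 1.2265 = 0.25 doublings, a ratio of 1.19.
- Relative to 0.696 doublings, this is 18% to 35% of the detectable effect.

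**Type I error under other assumptions.** Suppose there is no true effect, 50 completers per arm, and removed patients have cell-count changes 1.25 to 2 times those of patients kept. The standard error is 0.850 × √(1/n1 + 1/n2), using the numbers kept.

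- 20% v 10% removed, same prognostic difference in both arms: ratio 0.98 to 0.93, type I error 5.2% to 6.6%.
- 20% v 10% removed, difference only in the 20% arm: ratio 0.96 to 0.87, type I error 5.7% to 11.7%.
- 20% removed in both arms, but only one arm's removed patients differ: type I error 5.6% to 11.3%.
- Same share and same kind of patient removed in both arms: no bias.

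**Precision: excluding against keeping.** Noncentral t, true effect 1.62-fold in adherent patients, same non-adherent share f in both arms. Excluding leaves 50(1 − f) per arm. Keeping everyone leaves 50 per arm but shrinks the log effect to (1 − f) × 0.482 if non-adherers show no effect, or (1 − f/2) × 0.482 if they keep half of it.

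| f | n per arm, rule applied | Detectable ratio, rule applied | Power, rule applied | Power, all kept, no effect in non-adherers | Power, all kept, half effect |
|---|---|---|---|---|---|
| 0% | 50 | 1.62 | 80.2% | 80.2% | 80.2% |
| 10% | 45 | 1.66 | 75.9% | 71.5% | 76.1% |
| 20% | 40 | 1.71 | 70.8% | 61.3% | 71.5% |
| 30% | 35 | 1.78 | 64.8% | 50.3% | 66.6% |

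If non-adherers show no effect, 80% power with everyone kept needs about 61, 77 or 100 per arm at 10%, 20% or 30% non-adherence (normal approximation).

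**The case against.** The primary outcome is tissue cell counts and the question is mechanistic, so an interest in patients who actually took the drug is legitimate. Evaluability is fixed and documented before unblinding. Analysis by treatment group can be read as analysis by allocated group. The sentence does not name the primary analysis, and a separate analysis plan may define several populations. Excluding non-adherers can also give more power than keeping them.

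Some of this stands. Blinded decisions do prevent selection by someone who knows the code, and the power cost of keeping everyone is real. But blinding the decision does not help when treatment itself changes who adheres. Grouping by treatment says how patients are classified, not who is included. An analysis plan that kept everyone would contradict this sentence. Adherent-patient results can be reported as a supportive analysis.

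A reader might infer more than the document supports:

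- *That the rule removes everyone who leaves early.* That needs averaging over all 30 months. No period is given, and averaging over each patient's own time in the study is at least as natural a reading.
- *That data after withdrawal are barred from the treatment comparison.* One purpose is given for them; no other use is excluded.
- *That frequent oral-steroid courses or non-compliance automatically end participation.* They are listed as acceptable reasons, and the decision is left to the investigator.
- *That short- versus long-term fluticasone is the comparison most at risk.* These patients receive the same drug until month 6 and are split only then, whereas placebo and active arms differ throughout. Nothing in the document ranks the comparisons.
- *That recruitment makes no allowance for these exclusions.* The protocol includes 270 to finish with 200 but does not itemise the 70 losses (25.9%), and some non-compliers may already be among them.

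**Conclusion.** The rule is wrong as written. It is a post-randomisation exclusion that treatment can influence, it applies to the only analysis the protocol describes, and nothing elsewhere restores the patients it removes. This conclusion rests on the text and needs no assumption about adherence.

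The amount of bias is a different matter: neither its size nor its direction can be determined from the document. The 1.09- to 1.19-fold shift is only illustrative. It rests on an unsourced 30% v 10% imbalance and on removed patients differing by 0.5 to 1.0 SD, that is 1.53- to 2.34-fold, from those kept. The upper end of that gap exceeds the 1.62-fold target itself. Milder assumptions give type I error barely above 5%, and identical exclusions across arms would give no bias. The protocol does nothing to ensure that benign case.

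Loss of power is not the argument against the rule. Its removal can cost more power than it saves, and the case for removing it is validity.

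**What to change.** In Treatment compliance, replace the sentence by: *The primary analysis includes all randomised patients as allocated, whatever their compliance, using all biopsies and visits obtained, including those after study treatment is stopped. An analysis restricted to patients with at least 70% compliance over the period analysed is a sensitivity analysis.*

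In Statistical analyses, tie this to the two-stage allocation. The 0-6 month comparison uses the three groups first allocated. The short- versus long-term fluticasone comparison uses all patients allocated at month 6. Fluticasone patients who leave before month 6 have no second allocation and contribute to the first comparison only.

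In Withdrawal of patients, state that outcome data obtained after withdrawal enter the primary model.

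The cost is a wording change, one extra analysis, and an estimate diluted by non-adherence. That dilution may be more than slight. If non-adherers show no effect, power for 1.62-fold at 50 per arm is about 72% at 10% non-adherence and 61% at 20%, against 76% and 71% with exclusion. If they keep half the effect, the two approaches are about equal. The sponsor should state the non-adherence it expects and check that 50 per arm is still enough.
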